### Measures

Fig 1 is a flowchart summarizing this study’s procedures and outcome measures. The scheduled assessment of the study’s outcome measures is illustrated in Table 1. Data collection will be conducted every weekday during working hours, and flyers announcing the study and the benefits of participating in this study will be disseminated to all newly diagnosed head and neck cancer patients at the study’s focal institutions (within one month of their diagnosis) in order to ensure adequate subject enrolment to achieve the calculated sample size. This clinical trial protocol was written according to the “Standard Protocol Items: Recommendations for Intervention Trials 2013.”

**Fig 1 pone.0267887.g001:**
[figure not shown]
The flow diagram of the study procedures and outcome measures. ACT = acceptance and commitment therapy, MBSR = mindfulness-based stress reduction, AAQ-II = Acceptance and Action Questionnaire version II, PTGI-SF = Posttraumatic Growth Inventory-Short Form, HADS = Hospital Anxiety and Depression Scale, HOPE = Hope Scale, LOT-R = Life Orientation Test-Revised, FACT-H & N = Functional Assessment of Cancer Therapy–Head & Neck, T_0_ = pre-intervention assessment, T_1_ = immediately post-intervention at 8 weeks, T_2_ = 24 weeks after intervention.

**Table 1 pone.0267887.t001:** Scheduled assessment of the randomized control trial’s outcome measures.

	Enrolment	Allocation	Post-allocation	
Time	*-t* _ *1* _	*t*_*0*_ *(0 week)*	*t*_*1*_ *(8 weeks)*	*t*_*2*_ *(24 weeks)*
**Enrolment:**				
**Eligibility screen**	X			
**Informed consent**	X			
**Allocation**		X	X	X
**Interventions:**				
**(1) Acceptance and commitment therapy (ACT)**		X	X	X
**(2) Mindfulness-based stress reduction (MBSR)**		X	X	X
**(3) Controls (treatment-as-usual)**		X	X	X
**Assessments:**				
**(1) Socio-demographic and tumor characteristics data**		X		
**(2) Primary outcomes:**				
**“Posttraumatic Growth Inventory–Short Form” (PTGI-SF)**		X	X	X
**(3) Secondary outcomes:**				
**(a) “Dispositional Hope Scale”**		X	X	X
**(b) “Life Orientation Test–Revised” (LOT-R)**		X	X	X
**(c) “Acceptance and Action Questionnaire” (AAQ-II)**		X	X	X
**(d) “Hospital Anxiety and Depression Scale” (HADS)**		X	X	X
**(e) “Functional Assessment of Cancer Therapy–Head & Neck” (FACT-H & N)**		X	X	X

#### Sociodemographic and tumor characteristics

The sociodemographic characteristics which will be recorded from each participant include age, gender, ethnicity, marital status, education, and employment status. While the tumor characteristics which will be gathered from the participants are duration of cancer diagnosis, types of head and neck cancer, stage of cancer and modalities of cancer treatment received.

#### Primary outcome

*Posttraumatic growth*. The Malay version of the “Posttraumatic Growth Inventory–Short Form” (PTGI-SF) will be used to measure degrees of posttraumatic growth among participants. The PTGI-SF is a shorter version of the original PTGI, and it comprises 10 items, two of which measure each of the five PTG factors. The higher an individual’s PTGI-SF score, the more posttraumatic growth they have achieved. The PTGI can be substituted by the PTGI-SF with little loss of information [56]. The Malay version of the PTGI-SF was validated among the Malaysian cancer patient population, and it has good internal consistency with a Cronbach’s alpha of 0.887 and a Cronbach’s alpha of the five PTG factors ranging from 0.700 to 0.813 [57].

#### Secondary outcomes

*Quality of life*. The Malay version of “Functional Assessment of Cancer Therapy–Head & Neck” (FACT–H & N) will be used to assess quality of life among participants. FACT-H & N is a self-reported tool comprising 39 items and five subscales: *physical well-being* (seven items), *social/family well-being* (seven items), *emotional well-being* (six items), *functional well-being* (seven items), and *head & neck cancer additional concerns* (12 items). Each item is scored on a five-point Likert scale ranging from 0 (*not at all*) to 4 (*very much*). The higher an individual’s FACT–H & N score, the greater their QoL. The tool has also registered excellent psychometric properties [58]. FACT–H & N has been translated and validated among the Malaysian cancer patient population. All of its subscales have moderate to good internal consistency with Cronbach’s alphas ranging from 0.65 to 0.87 [59].

*Hope*. The Malay version of the “Dispositional Hope Scale” will be used to measure participants’ degrees of hope. The “Dispositional Hope Scale” is a self-rated, 12-item scale that assesses respondents’ hope levels. It comprises two domains: *agency* and *pathway*. Four of the scale’s 12 items assess agency, while another four items assess pathways. The four other items are fillers. Each item is scored using a Likert scale ranging from *definitely false* to *definitely true* [60]. The Malay version of the Scale was validated among the Malaysian cancer patient population, and it has good internal consistency with a Cronbach’s alpha of 0.716 [61].

*Optimism*. The Malay version of the “Life Orientation Test–Revised (LOT-R)” will be used to evaluate degrees of optimism among participants. The LOT-R is a self-rated tool comprising six items in two domains, *optimism* and *pessimism*. Each domain is made up of three items. The tool has good internal consistency and has been found to be stable over time [26]. The Malay version of the LOT-R was validated among the Malaysian cancer patient population, and it has acceptable internal consistency [62].

*Experiential avoidance*. The Malay version of the “Acceptance and Action Questionnaire” (AAQ-II) will be used to measure degrees of experiential avoidance or psychological inflexibility among participants. The AAQ-II is the questionnaire’s second version, revised from the original version, and it is shorter (seven items) while offering better psychometric consistency. Participants’ AAQ-II scores will be calculated by summing up the questionnaire’s seven items. Higher scores indicate higher levels of psychological inflexibility [63]. Validation of the Malay version of the AAQ-II has indicated that the tool has excellent internal consistency with a Cronbach’s alpha of 0.91, and it has been found to be a unidimensional scale that measures psychological inflexibility/EA [64].

*Depression and anxiety*. The Malay version of the “Hospital Anxiety and Depression Scale” (HADS) will be used to assess the severity of depression and anxiety symptoms among participants. The HADS is a 14-item, self-rated questionnaire with seven items in each of its subscales. Each item is scored from 0 to 3, and the total score for both the depression and anxiety subscales ranges from 0 to 21 per subscale [65]. The cut-off for depression cases is 8/21, and the cut-off for anxiety cases is also 8/21 [66]. The Malay version of the HADS has been validated among Malaysian breast cancer patients, and it exhibited acceptable to good internal consistency for its total score and subscales with Cronbach’s alphas ranging from 0.73 to 0.87 [67].

#### Other measures

The participants compliance to the interventions will be recorded as they will be requested to fill in electronic dairies regarding their performance of the home assignments and practice of the interventions at home. The reasons for absence from therapy sessions, dropouts and loss to follow up (such as loss of interest to participate, dislike of the intervention, not feeling well or death) will also be recorded.

### Data analysis

All of this study’s data analysis will be conducted using the Statistical Package for Social Sciences, version 26 (SPSS 26; SPSS Inc., Chicago, Illinois, USA). Initially, the baseline sociodemographic and tumor characteristics will be presented by randomized groups (ACT, MBSR, and control groups).

The mean difference in the primary outcome (total PTGI-SF score) for the three randomized groups (ACT, MBSR, and control groups) at each specific time point (pre-intervention [t_0_], post-treatment at 8 weeks [t_1_] and 24 weeks after intervention [t_2_]) will be assessed using one way analysis of variance (ANOVA) followed by false discovery rate adjustment. For the main pool analysis, mixed linear model will be employed for comparing the primary outcome (total PTGI-SF score) between ACT and control groups and between MBSR and control groups across the three time points (t_0_, t_1_ and t_2_), while controlling for stratification factors such as age and gender. The main effects of intervention in the groups and time points will be presented as estimated marginal mean and standard error of mean. The study’s primary analysis will follow the intention-to-treat (ITT) principle. The data analysis for the study’s secondary outcomes (quality of life, hope, optimism, depression, anxiety, and EA) will be conducted similarly to the primary outcomes’ calculation. In addition, 95% confidence interval will also be presented alongside the main effect. Statistical significance will be two-tailed and set to *p* < 0.05.

To handle any missing data, if the missing data represent less than 5% of the study’s total collected data, they will be ignored. If the missing data represent more than 5% but less than 40% of the total collected and are assumed to be randomly missing, then multiple imputation (restricted maximum likelihood estimation) will be performed using Stata 15. However, if the missing data represent more than 40% of the total collected data or are assumed to be missing either not randomly or completely randomly, then only the collected data will be used for the study’s analysis, and the missing data will be explained as a research limitation in any publications of the study’s findings [68].

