### Objectives

#### Primary objectives

Evaluate ACT’s efficacy in enhancing PTG among head and neck cancer patients compared to MBSR and a control (treatment-as-usual) immediately after the eight-week intervention and 24 weeks post-intervention compared to pre-intervention

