### Participants

This study’s participants will be recruited from the source population. This population includes all newly diagnosed head and neck cancer patients who have been treated only with surgery or who have not yet received treatment and who are registered under the oncology and otorhinolaryngology unit of the Advanced Medical and Dental Institute (AMDI) at the Universiti Sains Malaysia (USM) or the oncology and otorhinolaryngology unit of Universiti Kebangsaan Malaysia Medical Centre (UKMMC). The study’s sample size was determined based on G-Power 3.1.9.2 for analysis of variance (ANOVA). This sample size was calculated based on continuous responses to the posttraumatic growth inventory used in the study by Labelle et al. (2015) [48] with a medium effect size (0.15) and a two-tailed alpha of 0.05. The results of this calculation indicated that the current study requires a total sample of 93 for three equal-sized groups to achieve a power of 0.8. Anticipating a drop-out rate of 30%, we estimated a total sample size of 120 respondents and 40 respondents for each group.

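### The baseline (t0) ANOVA answers no trial question and, unless the false discovery rate adjustment is made within each visit, lowers the power of the t1 and t2 ANOVAs, by about 4 to 6 points at the plan's implied effect

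*Protocol article*

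**What the plan says.** The Data analysis section sets out two analyses of the primary outcome, total PTGI-SF score.

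- **Visit-wise tests.** Differences between the three arms are examined "at each specific time point (pre-intervention [t_0_], post-treatment at 8 weeks [t_1_] and 24 weeks after intervention [t_2"; they "will be assessed using one way analysis of variance (ANOVA) followed by false discovery rate adjustment". Neither the procedure nor the set of p-values it covers is named.
- **Mixed model.** The next sentence reads: "For the main pool analysis, mixed linear model will be employed for comparing the primary outcome (total PTGI-SF score) between ACT and control groups". It goes on to list MBSR versus control, with age and gender as covariates. ACT versus MBSR is not listed, and no false discovery rate step is stated for this model.

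The six secondary outcomes (quality of life, hope, optimism, depression, anxiety, experiential avoidance) are to be analysed in the same way. The significance rule is "Statistical significance will be two-tailed and set to *p* < 0.05".

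The Primary objectives section asks how ACT compares with both MBSR and control "immediately after the eight-week intervention and 24 weeks post-intervention compared to pre-intervention". The Participants section bases the sample size on ANOVA, "with a medium effect size (0.15) and a two-tailed alpha of 0.05", and concludes that the trial "requires a total sample of 93 for three equal-sized groups to achieve a power of 0.8". With 30% dropout expected, 120 are to be enrolled, 40 per arm.

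**The concern.** Allocation is random and t0 precedes treatment, so any difference between arms at t0 is due to chance. The null hypothesis is true by design, and the test has no bearing on efficacy. The objectives use t0 only as the reference from which change is measured.

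A test with a true null is not harmless inside a multiplicity family. Under Benjamini-Hochberg, a lone small p-value must fall below 0.05/3 = 0.0167 in a family of three, but only below 0.05/2 = 0.025 in a family of two. Real differences at 8 or 24 weeks can then miss significance because of a test that nobody needs. The same rule carries over to all six secondary outcomes.

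The visit-wise tests also matter in their own right. They are the only stated analysis in which ACT and MBSR enter the same comparison, and the primary objective asks for that comparison.

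**Working it through.** **1. The plan's sample size.** The 93 does not come from a one-way ANOVA: f = 0.15 would need 432, with power of only 0.23 at 93, and f = 0.25 would need 159. It does come from a repeated-measures ANOVA, within-between interaction, with f = 0.15, k = 3 groups, m = 3 measurements, sphericity 1 and an assumed correlation of 0.5:

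- λ = f²·N·m/(1 − ρ) = 0.0225 × 93 × 3 / 0.5 = 12.56
- df = (k − 1)(m − 1) = 4 and (N − k)(m − 1) = 180
- power = 0.811 at N = 93 and 0.796 at N = 90, so 93 is the smallest multiple of three that reaches 0.80.

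**2. Per-visit effect implied by that design.** Suppose the arms are equal at t0 and differ equally at t1 and t2. The time profile (0, 1, 1) has variance 2/9, so the interaction f equals the per-visit f times √(2/9). Hence per-visit f = 0.15/0.4714 = 0.318.

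**3. Simulated cost of t0 in the family.** Three correlated one-way ANOVAs were simulated, with no effect at t0, equal effects at t1 and t2, the two active arms equal, correlation 0.5, and Benjamini-Hochberg at 0.05 (100,000 runs per setting). The sizes are 120 enrolled, the 93 required, and 120 × 0.70 = 84 completers. Power at t1 is shown; t2 is within 0.2 points. Losses are taken from unrounded figures.

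| Per arm (total) | Per-visit f | Family t0, t1, t2 | Family t1, t2 | Loss (points) |
|---|---|---|---|---|
| 28 (84) | 0.318 | 63.5% | 69.6% | 6.2 |
| 31 (93) | 0.318 | 69.1% | 74.8% | 5.7 |
| 40 (120) | 0.318 | 82.4% | 86.4% | 3.9 |
| 28 (84) | 0.25 (assumed) | 38.7% | 45.4% | 6.7 |
| 31 (93) | 0.25 (assumed) | 43.6% | 50.4% | 6.8 |
| 40 (120) | 0.25 (assumed) | 57.1% | 63.5% | 6.4 |
| 28 (84) | 0.15 | 12.3% | 15.8% | 3.5 |
| 31 (93) | 0.15 | 13.9% | 17.8% | 3.9 |
| 40 (120) | 0.15 | 18.4% | 23.2% | 4.7 |

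The rows at 0.15 cover a reader who takes the stated effect size as a per-visit f. Correlations of 0 and 0.7, tried for some of the settings, give nearly the same losses.

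If only t1 has an effect (f = 0.318), the loss at t1 is 4.3 to 6.0 points. At t2, where there is nothing to detect, the rejection rate falls by only about 1.3 points.

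**4. Other readings of the family.** If all pairwise contrasts are pooled over visits, t0 makes nine contrasts instead of six. Power for an active arm versus control at t1, at f = 0.318, is then:

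- 28 per arm: 50.1% with nine, 56.9% with six
- 31 per arm: 56.3% and 63.0%
- 40 per arm: 71.6% and 77.0%

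The loss is 5.4 to 6.8 points. If the adjustment is made separately within each visit, t0 cannot affect t1 or t2 and the loss is zero.

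**5. Error control without t0.** With no effect at any visit, the chance of a false positive at t1 or t2 is 0.036 with t0 in the family and about 0.049 without it. Dropping t0 therefore stays within 0.05.

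**6. A borderline example.** Take p = 0.60 at t0, 0.02 at t1 and 0.30 at t2. The adjusted p-value at t1 is 0.02 × 3/1 = 0.06 with t0 in the family and 0.02 × 2/1 = 0.04 without it.

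**The case against.** The strongest reply is that the article never says which p-values form the family. With three arms, an ANOVA followed by an adjustment can also mean post-hoc pairwise comparisons corrected within each visit, and then t0 costs nothing. The Blinding section says that a statistical analysis plan will be in place before final unblinding, and a condensed article may leave the family to it. This stands as far as it goes: the power loss is conditional, and an undefined family is not in itself the defect. It does not remove the point, because the t0 test is in the stated text, in the same sentence as the other two tests and a single adjustment.

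The second reply is that the mixed model is named as the main pooled analysis and carries no stated false discovery rate step. This also stands. A reader might infer that the trial's main comparisons lose 6 to 7 points of power, and the document does not support that. ACT versus control and MBSR versus control in the mixed model lose nothing, and the upper figure needs a per-visit f of 0.25 that the document does not give. ACT versus MBSR has no other stated analysis, however.

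A reader might also infer that a chance significant result at t0 distorts the later tests by relaxing their thresholds. The effect is negligible. Given p < 0.05 at t0, the false-positive chance at t1 or t2 is 0.185 with t0 in the family and 0.171 without it. That is 1.4 points in about 5% of trials, or 0.07 points overall. Including t0 makes the plan conservative overall, not invalid.

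**Conclusion.** The point holds in a limited form. The t0 ANOVA tests randomised, untreated arms and addresses no objective. On the natural reading, or with pairwise contrasts pooled over visits, it takes power from the tests at t1 and t2. For the three-test family the loss per visit is about 4 to 6 points at the effect implied by the plan's own sample size, and up to about 7 at an assumed f of 0.25. It is zero if the adjustment is made within visits.

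These figures assume Benjamini-Hochberg at 0.05, visit correlation 0.5, equal variances and equal effects at t1 and t2. If only one visit has an effect, the loss is essentially confined to that visit. The simulations set the two active arms equal, so they give the power of the three-arm test and of active versus control, not of ACT versus MBSR directly.

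This is a modest inefficiency in the visit-wise ANOVAs. Validity and the mixed-model comparisons with control are not at issue.

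**What to change.** Remove the t0 ANOVA for PTGI-SF and for each secondary outcome. State that the false discovery rate family for an outcome is its t1 and t2 tests only or, if pairwise contrasts are meant, the six contrasts at t1 and t2. Report t0 scores by arm as mean and SD alongside the other baseline characteristics. Settle this before unblinding, so that the family cannot be chosen after the p-values are seen. The cost is a sentence or two in the Data analysis section, with no extra patients, data or analysis.

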MBSR is an eight-week, standardized group intervention comprising mindfulness meditation and gentle yoga designed to address stress, pain, and illness [40]. Cancer patients’ participation in MBSR has been shown to have increase in spirituality, PTG, self-compassion, and positive states of mind [41–47]. Studies have emphasized that MBSR increases PTG among participating cancer patients immediately after an eight-week intervention [44, 47, 48]. A meta-analysis of 29 studies with a total of 3,476 cancer survivors evaluated mindfulness-based interventions’ efficacy in facilitating mental well-being, revealing that MBSR significantly reduced depression, anxiety, stress, and fatigue while enhancing PTG, QoL, and mindfulness among cancer patients [49]. Moreover, MBSR has been reported to lower psychological distress and improve total, social, and emotional QoL among head and neck cancer patients [50]. To date, however, MBSR’s effect on cancer patients’ hope has not been investigated. Therefore, an investigation of MBSR’s effects on PTG, hope, optimism, depression, anxiety, and QoL among head and neck cancer patients would be interesting. Moreover, a comparison of MBSR’s efficacy compared to ACT would be valuable.

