### Support and ethics

This study has received approval from the Human Research Ethics Committee of Universiti Sains Malaysia (code: USM/JEPeM/21040321). The study will be conducted in compliance with the *Declaration of Helsinki* (1974) and its amendments, as well as the *Malaysian Good Clinical Practice Guidelines for Clinical Trials*. The institutional review board will be informed of any modification to the study’s protocol (such as its eligibility criteria, study procedures, outcome measures, scheduled interventions, and data analyses) in writing. This manuscript was written without any deviation from the original protocol submitted to the Human Research Ethics Committee of Universiti Sains Malaysia except we added more details to the title in this manuscript to make it more informative. The title of the original manuscript reads “Randomized controlled trial of acceptance and commitment therapy versus mindfulness-based stress reduction in newly diagnosed head and neck cancer patients”, while the title of this manuscript reads “Acceptance and commitment therapy versus mindfulness-based stress reduction for newly diagnosed head and neck cancer patients: A randomized controlled trial assessing efficacy for positive psychology, depression, anxiety, and quality of life”.

The principal investigator will lead the trial center and closely coordinate with the research coordinator and the site coordinator, participate in subject recruitment, and oversee the study’s consent procedures. A trial monitoring committee has been established. This committee is chaired by the principal investigator, and it will meet weekly to manage the study on a day-to-day basis, audit trial conduct, and prepare reports for submission to the Human Research Ethics Committee of Universiti Sains Malaysia. The trial’s data monitoring and auditing will be conducted by the AMDI’s clinical trial coordination unit at the Universiti Sains Malaysia—independently from the trial’s funder.

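### The main mixed model names ACT vs control and MBSR vs control but omits ACT vs MBSR, which the primary objective, every secondary objective and the title require

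*Protocol article*

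**What the plan says.** The Primary objectives section of the protocol article sets one objective: "Evaluate ACT’s efficacy in enhancing PTG among head and neck cancer patients compared to MBSR and a control (treatment-as-usual"), assessed "immediately after the eight-week intervention and 24 weeks post-intervention compared to pre-intervention". Each objective under Secondary objectives also names MBSR and control as the comparators for ACT. The title given under Support and ethics begins "Acceptance and commitment therapy versus mindfulness-based stress reduction for newly diagnosed head and neck cancer patients", and the introduction says that "a comparison of MBSR’s efficacy compared to ACT would be valuable".

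Data analysis describes two analyses of the total PTGI-SF score:

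- **Per-visit ANOVA.** The means of all three arms at each of t0, t1 and t2 "will be assessed using one way analysis of variance (ANOVA) followed by false discovery rate adjustment".
- **Main model.** A mixed linear model, controlling for age and gender and using all three assessments, "comparing the primary outcome (total PTGI-SF score) between ACT and control groups and between MBSR and control groups".

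The secondary outcomes are analysed in the same way. "Statistical significance will be two-tailed and set to" p < 0.05. No adjustment is attached to the mixed model, and neither t1 nor t2 is named as the primary visit.

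**The concern.** The comparison that defines the trial is missing from the analysis meant to deliver its main result. The text does not merely leave the contrasts open: it lists two, and ACT against MBSR is not one of them. Because the secondary outcomes follow the same scheme, the mismatch reaches every stated objective.

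If the report contains only the two contrasts against control, a reader who wants to know which therapy is better has only their two p-values to set side by side. One significant and one non-significant result is not evidence that the therapies differ. The chance of such a split when they are equally effective shows how far that reading could mislead.

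The second matter is error control. The only multiplicity step sits with the ANOVA, so the main model's contrasts are each judged at 0.05.

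**Working it through.** **1. Objective against analysis**

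| Comparison | Primary and secondary objectives | Main mixed model | Per-visit ANOVA |
|---|---|---|---|
| ACT vs MBSR | required | not named | arms included, pair not named |
| ACT vs control | required | named | arms included, pair not named |
| MBSR vs control | not listed | named | arms included, pair not named |

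A model fitted to all three arms could estimate ACT minus MBSR. The plan does not commit to reporting it.

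**2. Number per arm**

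The Participants section gives 93 evaluable patients in three equal groups, so 93/3 = 31 per arm, and 120 randomized, so 40 per arm. The figure 93 is reproduced by a group-by-time interaction test with f = 0.15, three groups, three measurements, correlation 0.5 and sphericity (the last two assumed). The noncentrality is f² × N × 3/(1 − 0.5), with 4 and 2(N − 3) degrees of freedom. Power is 0.811 at N = 93 and 0.796 at N = 90. The sample size therefore matches an omnibus test, not a pairwise contrast. By noncentral t at 31 per arm and two-sided 0.05, a pairwise difference of 0.5 SD has 49% power at a single visit, and 80% power needs about 0.725 SD.

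**3. Split results when the two therapies are equal**

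Assume both therapies differ from control by d SD at one visit. Each contrast is approximately normal with mean d√(n/2) and unit variance. The shared control arm and equal arm sizes give a correlation of 0.5. With p the power of one contrast and b the probability that both are significant at 0.05,

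P(exactly one significant) = 2(p − b).

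| d (assumed) | mean, n = 31 | p | b | exactly one, n = 31 | exactly one, n = 40 |
|---|---|---|---|---|---|
| 0.2 | 0.787 | 0.124 | 0.043 | 0.16 | 0.18 |
| 0.3 | 1.181 | 0.219 | 0.099 | 0.24 | 0.27 |
| 0.5 | 1.969 | 0.503 | 0.337 | 0.33 | 0.32 |
| 0.6 | 2.362 | 0.656 | 0.504 | 0.30 | 0.25 |
| 0.7 | 2.756 | 0.787 | 0.669 | 0.24 | 0.16 |
| 0.8 | 3.150 | 0.883 | 0.806 | 0.15 | 0.08 |
| 1.0 | 3.937 | 0.976 | 0.956 | 0.04 | 0.01 |

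**4. Familywise error of the two stated model contrasts, no true differences**

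- If independent: 1 − 0.95² = 0.0975 for two tests and 1 − 0.95⁴ = 0.185 for four.
- With the shared control, one visit: 0.09 (simulated, 400,000 draws).
- With the shared control, both t1 and t2: 0.174, 0.169, 0.161 and 0.149 for visit correlations of 0, 0.3, 0.5 and 0.7 (assumed), so about 15 to 17%.

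The pair ACT minus control and ACT minus MBSR also shares one arm and has the same correlation, so its figures are essentially the same.

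**5. Power cost of one possible rule**

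Simulation at one visit, 31 per arm, pairwise tests allowed only after a significant three-arm F test at 0.05. Power for ACT vs control:

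| d, ACT vs control | position of MBSR | no gate | gate | loss |
|---|---|---|---|---|
| 0.5 | midway | 0.49 | 0.37 | 12 points |
| 0.5 | equal to ACT or to control | 0.49–0.50 | 0.41 | 8 points |
| 0.6 | midway | 0.65 | 0.52 | 13 points |
| 0.6 | equal to ACT or to control | 0.65 | 0.58 | 7 points |

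**The case against.** The strongest reply is that ACT against MBSR is not wholly outside the plan. The per-visit ANOVA covers all three arms, and one plausible reading of its false discovery rate step is a set of adjusted pairwise comparisons that would include this one. It would be too strong to say that the two therapies are never compared. But the text does not say whether the step applies to pairs or to visits. The ANOVA also omits age and gender, looks at each visit separately rather than at change from pre-intervention, and is not the main analysis. It does not secure the primary comparison.

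A reader might also infer that MBSR against control has no place in the model. The documents do not support that. The abstract sets out to evaluate both therapies, the Rationale proposes assessing their effects against treatment as usual, and the Discussion describes the efficacy of both as the primary interest.

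A reader might further infer that the plan ranks the therapies by their significance against control. No section says so. The split-result figures describe a misreading that the omission invites, not a planned step, and they depend on effect sizes that the protocol does not give.

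On multiplicity, the objection has force. Separate model tests at t1 and t2 are inferred from the primary objective; the model sentence itself speaks of all three assessments together. A statistical analysis plan is mentioned under Blinding and not shown, and it may hold a testing rule. This limb is therefore a clarification. An unseen plan would not remove the contradiction between the stated objective and the stated contrasts.

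**Conclusion.** The mismatch stands: the main model omits the head-to-head contrast that the objectives and title call for, and the ANOVA does not clearly supply it. Significance against control is no substitute. With equal true effects of 0.5 to 0.7 SD and 31 per arm, about 24 to 33% of trials would show exactly one therapy significant; at 0.2 to 0.3 SD it would be 16 to 24%. These figures assume a single visit, a normal approximation and no gain from baseline adjustment, and they fall away for effects near 1 SD.

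The secondary point holds in limited form. The model's two contrasts have no stated adjustment, which gives about 9% familywise error at one visit and about 15 to 17% if both follow-up visits are tested. It would be wrong to call every primary-outcome test unadjusted, because the ANOVA has its own adjustment. Error rates above that range would need a third model contrast that the plan does not contain.

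**What to change.** In Data analysis, add ACT minus MBSR, with a 95% CI, to the same mixed model for the primary and the secondary outcomes. Make it and ACT minus control the primary contrasts, and keep MBSR minus control as supporting. This takes one more contrast from a model already planned, a few lines of text and no new data.

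State one multiplicity rule that covers the main model's primary contrasts and the visits at which they are tested. The method is the sponsor's choice: Holm, a fixed testing order, or an omnibus gate before pairwise tests would each serve. Whether one visit is made primary is also the sponsor's decision, since the objective gives both equal standing.

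The price is power per contrast. Under an omnibus gate at 31 per arm, ACT vs control loses roughly 7 to 13 points at 0.5 to 0.6 SD, depending on where MBSR lies. The ACT minus MBSR interval will be wide, because only a difference of about 0.725 SD has 80% power at a single visit with 31 per arm, even before any adjustment. The report should not read a non-significant difference as equivalence.
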